## Discussion

This study will be the first, to our knowledge, to investigate the effect of CrM on PPCS. We hypothesise that CrM supplementation will reduce the number and severity of PPCS measured though the self-reported post-concussion symptoms questionnaire called RPQ.

The short study period will prohibit conclusions on long-term impact. Furthermore, this study will not elucidate whether CrM is effective in the acute phase of a mild brain injury, such as concussion. This pilot study will therefore, in addition, serve as a methodological stepstone before investigating CrM as a possible treatment in larger populations.

If the large scaled RCT can elucidate that CrM is effective in the treatment of patients with PPCS, this could have a significant impact on the treatment courses offered by the healthcare system and followingly on the patients’ well-being.

## Dissemination

The investigators intend to submit their study findings for publication in peer-reviewed journals and to disseminate the findings via presentation at academic meetings/conferences.

## Ethics statement

This protocol was approved by the National Committee on Health Research Ethics (97508) and by the Danish Data Protection Agency 11.651. The study is registered at clinicaltrials.gov with the identifier NCT05562232.

The study will follow the ethical principles for medical research involving human subjects of the Declaration of Helsinki, adopted by the 18th General Assembly of the World Medical Association (42), which were last revised at the Association’s 64th General Assembly in Fortaleza, Brazil, in October 2013.

Before participation, the patients will be informed of the project and its purpose, both verbally and in writing. Response to the questionnaires constitute voluntary consent to participation; this will be applied for both baseline and follow-up. The participants will be required to sign a declaration of consent to ensure that they are fully aware of what they agree to participate in, the associated risks, and what they can gain from the study.

Participants will be free to withdraw from the study at any time without giving an explanation; if they choose to do so, their data will not be part of the final analysis. Data will be entered into the SurveyXact Online Clinical Trial Management System. Participants will receive a registration number as soon as they are deemed eligible for the study to ensure their anonymity. All personal identifiers will be removed or disguised during analysis to preclude personal identification.

There are no expected risks or harmful side effects from the study, as there no reported risks or harmful side effects of CrM supplementation, even with over 1 year of use (43). Furthermore, CrM supplementation is not expected to cause any discomfort for the participants.

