**Methods:**

The study is designed as a double-blinded randomised controlled trial. Study participants are found through neurological outpatient clinics in Denmark or through social media. They will be between 25 and 35 years of age, will have suffered from PPCS for 6–12 months prior to inclusion, and will have no comorbidities. The participants will be randomly allocated to either an intervention group (INT), placebo group (PLA), or control group (CG). Baseline data will be collected immediately after inclusion, and the study period will be 7 weeks. Follow-up data will be collected 1 week after the end of the study period. The primary outcome of the study is changes in RPQ score. Changes in weight and training status will be adjusted for as potential confounders.

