## Methods and analysis

### Study design

The pilot study will be performed as a randomised controlled trial in accordance with the SPIRIT guidelines (30). The study will include a convenience sample of 45 patients. The patients will be randomly allocated to either a control group (CG), placebo group (PLA), or intervention group (INT), with 15 patients in each group. As there has been too few randomised controlled trials (RCT) to establish a sample size through power calculations, this pilot study will be used to establish a sample size for a future RCT.

The study will be double blinded, that is, the participants, staff and investigators, will be unaware of treatment group the patients are allocated to. Furthermore, the process of randomisation will consist of a nutritionist not otherwise associated with the study who will randomly allocate each participant to a group until the desired sample size is reached. The nutritionist in charge of this step will also distribute either the placebo or the CrM to the participants in each of these groups.

CG will not receive any treatment other than usual treatment. PLA and INT will both receive a powder that must be ingested. PLA will receive a powder similar in appearance to CrM, but with no apparent nutritional value. INT will receive CrM.

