### Procedure

As both PLA and INT are the interventions, they will follow the same protocol for ingestion: 5 g per day for 7 weeks. All 5 g will be ingested at once (9). This protocol has been chosen instead of the more common 0.3 g/day for the first week ingested five times during the day (9). In other studies on CrM and the brain, 5 g per day was also the chosen strategy (31, 32). However, studies on CrM in the muscles indicate that both protocols illicit the same response at 28 days (9), and a loading phase is not required (33). Furthermore, some studies have used this protocol with creatine supplementation and reported increased cognitive function (27, 34). Our reason for choosing 5 g/day over 7 weeks was to increase compliance and decrease the risk of discomfort with high CrM intake. An intake five times a day for the first week is demanding and would likely result in some participants quitting the study.

At the mid-phase of the study, all baseline measurements will be repeated. The length of the intervention is 7 weeks. After the 7 weeks, all baseline measurements will be repeated (see Table 1). One week after last ingestion, the measurements will be performed one last time. At the week 8 appointment, every participant will be asked whether they thought they had received a placebo or CrM to determine how large an effect the placebo will have on the results.

**Table 1 tab1:** Study timeline.

	Pre (−1 week)			Intervention (7 weeks)			Post (+1 week)		
	CG	PLA	INT	CG	PLA	INT	CG	PLA	INT
Declaration of consent	X	X	X						
Height (m)	X	X	X				X	X	X
Weight (kg)	X	X	X	X	X	X	X	X	X
Concussion history	X	X	X						
Training status (hours/week)	X	X	X				X	X	X
RPQ (35, 36)	X	X	X	X	X	X	X	X	X
CrM						X			
Placebo powder					X				
Usual treatment				X	X	X			

CG will receive standard care. However, to our knowledge there is no commonly accepted description of standard care for PPCS in the literature. In general, these participants will be advised to continue with daily regular routines during the 7 weeks.

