### Statistics

Scales will be assessed for internal reliability, and Cronbach’s alpha will be estimated. We will apply unpaired t-tests to assess mean score differences at baseline and chi-square tests for sex distribution. Differences over time will be explored using paired sample t-tests. Applying Cohen’s d, effect sizes will be derived by calculating mean differences and standard deviations. To assess differences in outcomes between groups, we will employ linear mixed regression. All statistical analyses will be performed using SPSS for Windows (IBM Corp., 2018., Version 25.0., Armonk, NY).

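### The rule excluding all data of anyone who withdraws discards baseline and mid-phase RPQ scores that the planned mixed model could use, and can bias the group comparison

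*Protocol article*

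**What the plan says.** - **Ethics statement.** "Participants will be free to withdraw from the study at any time without giving an explanation"; and "if they choose to do so, their data will not be part of the final analysis". The exclusion is not limited to people who ask for their data to be removed, and no other section limits it.
- **Study design.** "The study will include a convenience sample of 45 patients", "with 15 patients in each group". The groups are usual care only (CG), placebo powder (PLA) and creatine (INT). No power calculation was made, and the results are to set the sample size of a later trial.
- **Abstract, Methods.** "The primary outcome of the study is changes in RPQ score".
- **Procedure and Table 1.** RPQ is measured at baseline, during the intervention period and one week after the last intake. The Procedure text repeats all baseline measurements at mid-phase and again after 7 weeks.
- **Statistics.** "To assess differences in outcomes between groups, we will employ linear mixed regression". Cohen's d is to be derived from mean differences and SDs. The section names no analysis set.

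**The concern.** Someone who leaves after the mid-phase visit has a baseline and a post-baseline RPQ. A linear mixed model can use that record and is valid if missingness depends only on observed data. The Ethics statement removes the record before the model is fitted. The protocol therefore chooses a method that tolerates incomplete follow-up and then withholds the incomplete follow-up from it.

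This matters if leaving is related to symptoms and is unequal between arms. Both are plausible. The outcome is self-reported symptoms, so feeling no better is a reason to leave that is tied to the outcome. CG participants receive no powder and can tell their allocation, whatever the protocol says about blinding.

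At stake are the between-group estimate, the precision of very small arms, and the SD and effect size on which the next trial will be planned. Because the rule is stated beside the consent terms, a later analysis plan could not simply set it aside.

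**Working it through.** **Inputs from the protocol.** Three arms of 15: 3 × 15 = 45, which reproduces the stated total. There is no power-based figure to reproduce, and no withdrawal rate, SD or alpha is given.

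**Assumptions.** No true difference between arms; change in RPQ in SD units, with lower being better; withdrawal rates and correlations as stated below.

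**1. Yardstick.** The standard error of a difference between two arms of n is √(2/n).
- n = 15: √(2/15) = 0.37 SD.
- n = 12: √(2/12) = 0.41 SD.
- For an assumed true difference of 1 SD (two-sided 0.05, normal approximation), power falls from 0.78 to 0.69.

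Retained mid-phase data recover only part of this loss.

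**2. Two estimators compared by simulation.**
- Deletion: the difference in mean final change among those who stay.
- Retention, a regression form of what a mixed model does: for each arm, estimate = ȳ(stayers) + s × [m̄(all) − m̄(stayers)]. Here y is the final change, m the mid-phase change and s the pooled slope of y on m.

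**3. Withdrawal depends on the observed mid-phase change.** The model is logistic with slope 2 per SD, mid-to-final correlation 0.6 and 6,000 runs. Twenty per cent of 15 is 3 people.

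| Withdrawal, INT / PLA | Bias, deletion (SD) | Bias, retention (SD) |
|---|---|---|
| 10% / 0% | −0.08 | +0.007 |
| 20% / 0% | −0.15 | +0.003 |
| 20% / 10% | −0.07 | −0.002 |
| 30% / 10% | −0.14 | +0.004 |
| 20% / 20% | 0.00 | 0.00 |
| 30% / 30% | −0.01 | 0.00 |

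Negative values favour INT. The type I error of a t-test on those who stay is at most about 0.067. Here the deletion rule creates the bias and retention removes it.

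**4. Withdrawal depends on the unobserved final outcome.** Exactly 3 leave one arm and none the other. The withdrawal score is correlated c with the final outcome, and the mid-to-final correlation is 0.5 to 0.7.
- Deletion: 0.16 SD at c = 0.5, 0.23 at c = 0.7 and 0.33 at c = 1 (the three worst leave).
- Retention over the same settings: about 0.09 to 0.26 SD, that is 53% to 78% of the deletion bias.
- Share due to the rule: from 0.16 × (1 − 0.78) ≈ 0.04 SD to 0.33 × (1 − 0.53) ≈ 0.15 SD. It is smallest when both correlations are 0.5. It is largest when c = 1 and the mid-to-final correlation is 0.7.

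In step 4 most of the bias comes from the withdrawal itself, and only the remainder from the deletion rule.

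**5. Direction.** If worse-off INT participants leave, INT looks better. If worse-off CG participants leave, CG looks better and the error runs against INT.

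**The case against.** The strongest case against acting is that this is a convenience-sample pilot without a power calculation, that PLA and INT share one intake schedule under blinding, and that equal withdrawal gives no bias. The share of bias due to the rule is also well below one standard error. All of that stands, and it limits the severity. It does not justify the rule, because the protocol also states an efficacy hypothesis and passes its estimates to the next trial.

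Several stronger readings are tempting, and the protocol does not support them:

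- **The plan expects its own intake burden to make people quit.** The sentence "An intake five times a day for the first week is demanding and would likely result in some participants quitting the study" concerns a schedule the authors decided against. They chose theirs partly to improve compliance. It is no evidence of expected withdrawal under the adopted schedule.
- **CG gets nothing.** CG continues usual care; what it lacks is the powder.
- **The analysis is completers-only.** The rule covers people who withdraw from the study. Someone who misses a visit or stops the powder without withdrawing is not covered and can stay in the mixed model.
- **The rule hides retention.** Excluding data from the analysis does not prevent withdrawals being counted and reported by arm.
- **Bias of 0.33 SD and type I error of about 15%.** These need exactly the three worst patients to leave one arm and nobody to leave the other. They also measure the total effect of such withdrawal, most of which retention would not remove.

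**Conclusion.** The point holds as a rule that is explicitly stated and badly chosen; it is not a detail left to an analysis plan. It should be fixed, but it is not a fatal defect. Bias is conditional: it needs withdrawal that is related to symptoms and unequal between arms, and its direction depends on which arm loses its worse-off participants.

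With 3 of 15 leaving one arm and none the other, the rule itself adds roughly 0.04 to 0.15 SD, against a standard error of 0.37 SD. That range rests on assumed rates and correlations, and a steeper dependence on mid-phase scores would raise it. Retention cures the bias when withdrawal follows observed mid-phase scores and only reduces it when withdrawal follows the unseen final outcome. Removing an outcome-related tail also distorts the SD and Cohen's d handed to the future trial.

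**What to change.** Replace the sentence in the Ethics statement with, for example:

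> Data collected up to withdrawal are retained and analysed in the randomised group in the mixed model; data are excluded only if the participant explicitly asks for this.

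Amend the participant information to match and notify the ethics committee. For anyone already enrolled under the present wording, either honour it or obtain renewed consent. The right to withdraw without explanation is untouched.

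The cost is one amended sentence, the matching information text and a notification. It should be done early, because data given under the present promise cannot simply be brought back at analysis.
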